# Increasing Children’s physical Activity by Policy (CAP) in preschools within the Stockholm region: study protocol for a pragmatic cluster-randomized controlled trial

**DOI:** 10.1186/s13063-022-06513-4

**Published:** 2022-07-19

**Keywords:** Physical activity, Policy, Intervention, Cluster-randomized controlled trial, Preschool, Accelerometer-based measurement

## Abstract

**Background:**

Systematic reviews suggest that preschool environmental/organizational changes may be effective in increasing physical activity (PA) levels of preschool children, but evidence is scarce regarding feasible, effective, and equitable interventions that can be scaled up. Specifically, it is essential to understand whether introducing a multicomponent organizational change in terms of policy in the preschool context may be beneficial for children’s PA levels and concomitant health outcomes. To bridge this knowledge gap, our main aim is to examine the feasibility and effectiveness of a policy package in increasing PA levels in preschool children, using a large-scale pragmatic cluster-randomized controlled trial.

**Methods:**

This proposed study is a pragmatic cluster-randomized controlled trial with two conditions (intervention and control with a 1:1 ratio) with preschools as clusters and the unit of randomization. We aim to recruit approximately 4000 3–5-year-old children from 90 preschools and retain more than 2800 children from 85 preschools to provide adequate statistical power for the analyses. The intervention to implement is a co-created, multicomponent policy package running for 6 months in preschools randomized to intervention. Change in accelerometer measured PA levels in children between intervention and control from pre- and post-intervention will be the primary outcome of the study, while secondary outcomes include health outcomes such as musculoskeletal fitness, psychosocial functioning, and absence due to illness in children among others. Implementation will be studied carefully using both quantitative (dose, fidelity) and qualitative (interview) methodologies. The change in primary and secondary outcomes, from pre- to post-intervention, will be analyzed with linear mixed-effect models (to allow both fixed and random effects) nested on a preschool level.

**Discussion:**

This is a large-scale co-creation project involving the City of Stockholm, childcare stakeholders, preschool staff, and the research group with the potential to influence more than 30,000 preschool children within the Stockholm area. The study will add reliable evidence for the implementation of PA policies at the organizational level of preschools and clarify its potential effect on objectively measured PA and health markers in children.

**Trial registration:**

ClinicalTrials.govNCT04569578. Prospectively registered on September 20, 2020.

**Supplementary Information:**

The online version contains supplementary material available at 10.1186/s13063-022-06513-4.

## Background

Low levels of physical activity (PA) are a growing global concern [1] and efforts to increase PA are imperative for children of preschool age [2]. Total PA and moderate to vigorous PA (MVPA) are positively associated with the healthy development of young children (< 5 years) [3]. For example, childhood PA is positively associated with musculoskeletal fitness, cardiometabolic health, and psychosocial health [3]. In contrast, excessive sedentary time (ST) in youth is associated with increases in markers of cardiometabolic disease risk [4]. Consistent data show that low levels of musculoskeletal fitness in children are longitudinally associated with low bone mass density, adiposity, metabolic risk factors, and premature mortality [5]. In addition, the healthy PA habits developed during early ages may track to later stages of life [6, 7]. Consequently, the assessment of PA and musculoskeletal fitness in youth is relevant from a public health perspective.

Despite the known benefits of PA, children in general engage in low levels of PA and their PA tends to decrease with age [8]. A recent Swedish accelerometer-based national survey showed that only 23% of adolescent girls and 43% of boys reached the recommended level of a minimum of 60 min of daily MVPA [9]. Moreover, low accelerometer measured PA levels have been shown in preschoolers, as highlighted by a study of approximately 1000 Swedish preschool children [10].

Higher intensity PA (e.g., MVPA) is a major determinant of physical fitness in children [11]. In addition to the observed low levels of PA among preschoolers, physical fitness among youths is declining globally [12] and in Sweden [13]. Notably, the decline in fitness level is more pronounced in countries with higher income inequality [12] where PA levels are lower in socioeconomically disadvantaged communities [9]. Therefore, it is vital to develop strategies to promote PA in individuals with various socioeconomic backgrounds, equitably as early as in preschool age.

The preschool setting presents unique opportunities to promote PA and health since the children are very young and habits can be more easily acquired. This makes this setting even more promising than the school setting. For example, preschool PA routines and practices can influence a major proportion of waking hours in children, since children in Sweden generally spend a large part of their waking hours at preschool. In addition, approximately 95% of Swedish 3–5-year-old children attend preschools regardless of their parent’s socioeconomic status (SES) [14]. Therefore, preschool interventions may offer each child an equitable opportunity in forming early healthy PA behaviors.

Moreover, preschools provide appropriate conditions to explore associations between PA, time spent outdoors and absence due to illness in children, which are important parameters from a public health as well as an economic perspective. For example, time spent outdoors at the preschool may contribute to health benefits through increased PA in children [15]. In addition, increasing time spent outdoors may reduce person-to-person transmission of infections, since children brought together in close environments, such as a preschool indoor environment, are mutually exposed to the transmission of pathogens [16]. It is possible that PA acts a mediator of the link between outdoor activities and absence due to illness in children [17]; reduced infection rates could be achieved by reducing transmission of disease as well as reducing host susceptibility through the beneficial health effects of PA. However, the association between outdoor stay and absence due to illness in children is currently unclear, as outdoor time has been shown to both reduce [18] and increase [19] absence due to illness in children. In addition, research has shown equivocal effects from PA on absence due to illness in children [20]. Nonetheless, it is conceivable that outdoor time impacts on infection rates by both decreasing the opportunity of transmission and by reinforcing immunity defense via PA. However, it is possible that outdoor activities also impact other morbidity (e.g., accidents and traumas); hence, the net effect may be concealed.

Previous meta-analyses and reviews of PA interventions in preschoolers indicate that interventions are likely to be effective when inducing environmental/organizational change in the preschool setting, targeting multicomponent factors such as integrated structured PA time, and ensuring unstructured outdoor time and instructions to preschool teachers on how to lead structured activity [21, 22]. Although policies may be potentially modifiable organizational factors in preschools, introducing preschool policy can be challenging since preschool policies often suffer from unclearness, poor implementation, and lack of tools for follow-up and measures of compliance [23, 24]. Furthermore, few previous studies have explored the association between preschool PA policies and children’s PA levels [25–27]. An observational study from Sweden has demonstrated higher PA levels in children enlisted in preschools with a PA policy [27]. This result is in line with findings from other countries [25, 26]. However, only a quarter of all participating preschools in the Swedish study had a PA policy [27]. In general, the few existing randomized controlled trials within the field suffer from small sample sizes and limited intervention duration [21, 22]. A systematic review by Wolfenden et al. focused on PA polices within preschool setting reported little benefit on PA outcomes [28]. This may be a result of the lack of an evidence-based policy, the policy not being adapted to the context, the absence of a theory base, and various challenges in implementation of the policy [28]. Similarly, a recent study by Carson et al. that employed a quasi-experimental pre-post design with accelerometer-based PA measurement also demonstrated no effect of preschool policy on PA outcomes of preschool children [29]. Accordingly, Wolfenden et al. emphasized the current scarcity of evidence and that well-design pragmatic randomized controlled trials with sufficient sample size and valid measurements are imperative to evaluate policy in a real-world setting [28]. To the best of our knowledge, there is only one ongoing pragmatic randomized trial testing preschool PA policy’s effect on PA levels of children [30]. In contrast to our trial which employ accelerometers to assess levels of PA, the ongoing trial by Nathan et al. use educator-reported PA [30]. Notably, although preschool teachers are key components in the implementation of policy, the policy’s effect on preschool teachers’ PA and its possible implications on parameters such as sick leave has not been studied previously. Such knowledge could add to the understanding of preschool PA policies and how they may affect change in PA. In addition, the equity perspective of PA interventions has been largely neglected previously [31].

### Objectives

The primary aim of the increasing ***C****hildren’s physical*
***A****ctivity by*
***P****olicy* (CAP) study is to evaluate the feasibility and effectiveness of implementing PA policies in preschools on preschool children’s PA levels. The secondary aims of the study include exploring the effectiveness of PA policy on preschool children’s (i) sedentary time, (ii) screen time, (iii) musculoskeletal fitness, (iv) sleep, (v) adiposity, (vi) psychosocial functioning, (vii) absence due to illness in children, and (viii) children’s PA opportunity outside preschool time such as active transport and organized sports participation as well as on preschool teachers’ (i) physical activity levels, (ii) sedentary time, (iii) sleep, (iv) adiposity, and (v) sick leave in teachers. We will also investigate the implementation of the policy and how this policy can be normalized into preschool teachers’ regular practice by exploring (i) dose and fidelity of the implementation, (ii) facilitators and barriers in implementing the preschool policy, and (iii) sustainability of the policy.

### Hypothesis

The hypothesis is that implementing PA policies in preschools will increase PA in young children and preschool teachers equitably across districts with diverse SES. We further hypothesize that implementing PA policies will lead to improvements in children’s musculoskeletal fitness, psychosocial functioning, sleep and reduce sedentary time, screen time, and absence due to illness in children and sick leave in preschool teachers. The policy may also influence preschool children’s PA opportunities outside preschool time such as increases in active transport. However, adiposity is hypothesized to not be affected as meta-analysis data showed limited evidence for an association between PA and adiposity among preschool children [32].

## Methods/design

### Study design and setting

The current study is a pragmatic cluster-randomized controlled superiority trial with two conditions (intervention and control) with preschools as clusters and the unit of randomization. A cluster randomization design was chosen because the intervention targets policy on the organizational level in preschools and preschools are natural clusters. Units of observations are preschool children and preschool teachers. The report of this trial protocol is guided by SPIRIT reporting guidelines [33] and we provide the detailed SPIRIT Checklist (see SPIRIT Checklist). We will report the findings of the trial according to guidelines outlined in the CONSORT extension for cluster-randomized trials [34]. The current study is being conducted in the Stockholm region of Sweden. To date in the Stockholm region, there are 30,969 children (1–5 years old) enrolled in a total of 539 public preschools (personal communication with Stockholm region representative, 2020-06-15). The Stockholm region can be divided geographically and administratively into 13 districts which vary in size, number of preschools, children, and resources.

### Ethical approvals and informed consent

Ethical approval has been obtained from the Swedish Ethical Review Authority (Dnr. 2020-03002), and this study has also been pre-registered at a database for clinical studies (https://clinicaltrials.gov) with reference number: NCT04569578. All items from the World health Organization Trial Registration Data Set can be found ClinicalTrials.gov. The registration of the study was completed before the recruitment of participants. The project coordinator contacted participating preschool staff about project information and provide information to distribute to the potential participating children and parents (Additional file 1). The project rationale, process, and motivational/explanatory videos are also available from the project website (Website in Swedish Rörelseprojektet (regionstockholm.se)). An informed consent form can be downloaded directly from this project website and physical copies of the informed consent form are available at the respective preschool. Written informed consent signed by parents of the participating children and participating preschool teachers will be gathered at the respective preschools. The informed consent will then be collected by one of the trained field workers prior to the baseline measurement. After collection, data in the informed consent will be manually typed into a database and stored securely on servers within the Center for Epidemiology and Community Medicine, Stockholm County Health Care Area (SLSO).

### Sample size

The required sample size to obtain a statistical power of 0.90 was projected with a change in MVPA as the main outcome variable and by using the means and standard deviations of the aforementioned observational preschool study assessing PA [27]. A 5-min change in MVPA has been suggested in previous meta-analysis to be a reasonable target of clinical importance [35]. Assuming an effect size of 5 min MVPA, an intra-preschool correlation of 0.2, a standard deviation of 25, coefficient of variation of 0.3 (average preschool size of 35 children 3–5 years), and approximately 2800 children (from 85 preschools) should be retained.

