### Intervention development and theory base

The interest for the intervention began when the previously mentioned observational study found a positive association between having a formalized PA policy in preschools and children’s PA levels [27], which attracted attention from politicians and stakeholders in the City of Stockholm. Realizing the potential of policy to increase PA among preschool children, the stakeholders took a formal political decision that all public preschools in the Stockholm region should implement a formalized PA policy. This decision is documented in the public preschools’ financial steering plan and implies that all public preschools in the Stockholm region should exert effort and financial resources in the implementation of a PA policy. In addition, a policy package should be developed and evaluated to provide a “model” for preschools to understand what PA policies to implement and effective strategies for implementation. The intervention policy package has been developed in co-creation among the research group, municipal childcare stakeholders, district officers from the 13 Stockholm region districts and a reference group consisting of preschool principals and teachers. The policy package has been discussed and acknowledged among all co-creators to increase the engagement, buy-in, feasibility, relevance, and sustainability of the intervention policy package as recommended by a previous meta-analysis on the effectiveness in co-creation of research [36]. The Behaviour Change wheel [37] was chosen as a theory base to understand and reflect on essential conditions (capacity, opportunity, and motivation) for behavior change in relation to the intervention’s functions and policy category. (The detailed logical model of theory of change for the policy package intervention based on behavioral change wheel can be found in Additional file 4 theory of change).

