### Statistical analysis

The baseline demographic characteristics of the participants will be summarized descriptively. Dropout participants’ characteristics will be explored by comparison to the non-dropouts. Fidelity and dose of implementation will be summarized as a score (fidelity × number of weeks of compliance). The change in PA levels and secondary outcomes, from pre- to post-intervention, will be analyzed with linear mixed-effect models (to allow both fixed and random effects) nested on the preschool level. The linear mixed-effects model can test several aspects of the study effects, e.g., effects over time inside a group, and groups against each other at a given time (e.g., intervention vs. control at 6-month follow-up). Subgroup analyses will be conducted to analyze the effect of the intervention in relation to socioeconomic aspects. Furthermore, we aim to explore if the COVID-19 pandemic has modified any implementation aspects of the intervention (via questionnaires on how various routines including outdoor time, hygiene aspects at preschools, homestay, and transportation mode to/from preschool have changed following the COVID-19 pandemic).

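### The stated 90% power for change in MVPA is not supported: SD 25 and ICC 0.2 are not labelled as level or change, and used as given they yield about 47%

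*Protocol article*

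**What the plan says.** The Sample size section makes its projection "with a change in MVPA as the main outcome variable and by using the means and standard deviations of the aforementioned observational preschool study". The listed inputs begin "Assuming an effect size of 5 min MVPA" and continue with "an intra-preschool correlation of 0.2, a standard deviation of 25". They also include a coefficient of variation of cluster size of 0.3 and an average of 35 children per preschool. The stated power is 0.90 with about 2800 children retained from 85 preschools. Alpha and sidedness are not among the listed inputs.

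The Background describes the source study by levels: "An observational study from Sweden has demonstrated higher PA levels in children enlisted in preschools with a PA policy [27". The section on intervention development says that "the previously mentioned observational study found a positive association between having a formalized PA policy in preschools" and the children's PA levels. Neither place says that children in that study were measured twice.

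The trial itself measures children at baseline and at 6 months. Under Statistical analysis, "The change in PA levels and secondary outcomes, from pre- to post-intervention, will be analyzed with linear mixed-effect models", nested on preschool. The same section adds that the model can also compare the groups at one time point, such as 6 months.

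**The concern.** A change has a different variance from a single measurement. The conversion depends on two baseline-to-follow-up correlations: one between preschool means and one between children within a preschool. The SD of a change equals the SD of a level only for particular values of these correlations. The ICC is unchanged only if the two correlations are equal. The article names change as the outcome and takes its SD from a study described by levels, with nothing linking the two. A reader therefore cannot tell what SD 25 and ICC 0.2 describe.

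What is at stake is the stated 90% power. It tells readers how likely the trial was to detect the 5-minute effect that the article treats as clinically important. If the inputs do not deliver it, the figure misdescribes the design.

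**Working it through.** **Inputs.** From Sample size: effect 5 min, SD 25, ICC 0.2, CV 0.3, 2800 children, 85 preschools, power 0.90. From Randomization and blinding: 1:1 allocation. Assumed: two-sided alpha of 5%. Mean cluster size m = 2800/85 = 32.94.

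**Formulas.**
- Design effect: DE = 1 + ((1 + CV²)m − 1) × ICC
- Standard error: SE = SD × √(4 × DE/2800)
- Power = Φ(5/SE − 1.96)

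**Step 1: the plan's own figure, with the inputs as given.**
- Without clustering, 4 × (1.960 + 1.282)² × 25²/5² ≈ 1051, or 1052 as 526 per arm.
- DE = 1 + (1.09 × 32.94 − 1) × 0.2 = 7.98.
- Children needed: 1052 × 7.98 ≈ 8,400, in about 255 preschools (8,400/32.94).
- At 2800 children, SE = 25 × √(4 × 7.98/2800) = 2.67. Then 5/2.67 = 1.87 and power = Φ(−0.09) ≈ 47%.

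The stated 2800 in 85 is not reproduced. A one-sided 5% test gives about 59%. Even one-sided 5%, 80% power and CV 0 together need about 4,580 children. At SD 25, 2800 children give 90% power only if the ICC is about 0.048.

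**Step 2: the inputs read as level inputs.** The level variance is 625, of which 125 is between preschools and 500 within. Let rb be the preschool-level correlation and rw the child-level correlation.
- Unadjusted change score: between 2 × 125(1 − rb), within 2 × 500(1 − rw).
- Baseline-adjusted, an approximation that adjusts separately at each level: between 125(1 − rb²), within 500(1 − rw²).

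For each model, SD is the square root of the sum and ICC is the between part over the sum. With 85 preschools, 2800 children and rw = 0.5:

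| rb | SD of change | ICC of change | Power, change score | Power, baseline-adjusted |
|---|---|---|---|---|
| 0.2 | 26.5 | 0.29 | 33% | 49% |
| 0.5 | 25.0 | 0.20 | 47% | 58% |
| 0.7 | 24.0 | 0.13 | 65% | 73% |
| 0.8 | 23.5 | 0.09 | 79% | 84% |
| 0.85 | 23.2 | 0.07 | 87% | 91% |
| 0.9 | 22.9 | 0.05 | 94% | 97% |

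Example for rb = 0.9, change score: variance 25 + 500 = 525, SD 22.9, ICC 25/525 = 0.048, DE = 1 + 34.91 × 0.048 = 2.66. SE = 22.9 × √(4 × 2.66/2800) = 1.41, and power = Φ(3.54 − 1.96) ≈ 94%.

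Example for rb = 0.2, baseline-adjusted: variance 120 + 375 = 495, SD 22.2, ICC 0.242, DE = 9.46. SE = 2.59, and power = Φ(1.93 − 1.96) ≈ 49%.

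The child-level correlation matters much less. For the change score, moving rw from 0.3 to 0.7 shifts power only from 32% to 33% at rb 0.2, from 45% to 48% at rb 0.5, and from 91% to 97% at rb 0.9.

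**The case against.** **Level inputs may be apt.** Neither SD 25 nor ICC 0.2 is labelled, and only means and SDs are attributed to the observational study. A reader might infer that the ICC also comes from that study and that both figures are stated to be for levels. The article does not say so: the level reading of the SD is an inference, and the ICC has no stated source. The Statistical analysis section also allows a between-group contrast at 6 months, for which level inputs would be right. This stands. It does not rescue the 90%, because a single-time contrast with these inputs is the 47% case.

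**The low end depends on the model.** The article does not fix an unadjusted change score. With baseline adjustment the 33% becomes about 49%. This also stands, so the range must be shown for each model.

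**The two ICCs need not differ.** The ICC of change equals the ICC of levels whenever the two correlations are equal. Both SD and ICC carry over unchanged only when both correlations are 0.5. Correct, and it limits the point to inputs whose meaning is unclear.

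**A journal article condenses.** A repeated-measures correlation is often left to a fuller document, and its absence alone would be no finding. But the article prints a power and the inputs offered for it. Those inputs do not give that power as they stand. On the level reading they give it only with a high correlation that is not stated.

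**Recruitment has moved on.** The Fig. 1 caption reports 3775 children agreeing to take part and 124 preschools measured at baseline. With the planned 30% loss (3775 × 0.70 ≈ 2,640 children, 21.3 per preschool), SD 25 and ICC 0.2 give about 60%. That is better than 47% but still not 90%.

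**Conclusion.** The concern holds as one about an unsupported power statement. If SD 25 and ICC 0.2 describe the analysed quantity, power at 2800 children in 85 preschools is about 47%, and 90% needs about 8,400 children. If they describe levels, power is about 33% to 94% for an unadjusted change score, or about 49% to 97% with baseline adjustment, as the preschool-level correlation goes from 0.2 to 0.9. The stated 90% is reached only at a correlation of roughly 0.85 to 0.9. These figures assume a two-sided 5% test, a child-level correlation of 0.5 and a normal approximation.

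A reader might go further and conclude that the trial is shown to be too small. The documents do not support that: if preschools keep their ranking closely over 6 months, 90% or more is attainable on the level reading. What is established is that the article does not give the grounds for its 90%.

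**What to change.** In the Sample size section, or in a published correction or update to it:

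1. Label SD 25 and ICC 0.2 as inputs for a level or for a 6-month change.
2. Give the source of the ICC, the baseline-to-follow-up correlations assumed at preschool and child level, and the alpha and sidedness.
3. Replace the stated 90% with the power those inputs deliver, shown as a range over the preschool-level correlation and for the model to be used (change score or baseline-adjusted).

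A pooled estimate of the SD and ICC of change, made without arm labels from the two measurement waves, may be reported as a supplement. It would not show what was planned and should not be presented as if it did.

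The cost is a rewritten paragraph and a short calculation, plus one blinded variance estimate if the supplement is wanted. The stated power becomes a range. Enrolment does not change.

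### The printed sample-size inputs give about 46% power without baseline adjustment, not the stated 90%; an input or the power is wrong, or an input was left out

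*Protocol article*

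**What the plan says.** The Sample size section opens: "The required sample size to obtain a statistical power of 0.90 was projected with a change in MVPA as the main outcome variable". It takes means and standard deviations from the group's earlier observational preschool study and continues: "Assuming an effect size of 5 min MVPA", then "an intra-preschool correlation of 0.2, a standard deviation of 25, coefficient of variation of 0.3". The average preschool size is 35 children, and about 2800 children from 85 preschools are to be retained.

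The Methods paragraph of the Abstract shows that this is the whole-trial total after losses: the plan is to "retain more than 2800 children from 85 preschools to provide adequate statistical power for the analyses". Randomization and blinding gives 1:1 allocation of preschools within districts. Study population and recruitment puts expected loss at about 30%, which is the step from about 4000 recruited to 2800 retained. The article states no alpha, no sidedness and no correlation between baseline and follow-up. It also does not say whether 25 is the SD of MVPA at one time or of its change.

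**The concern.** The section publishes both its inputs and its result, so a reader can recompute it, and the result does not follow. An ICC of 0.2 with about 33 children per preschool inflates the variance roughly eightfold. A trial of 2800 children then carries the information of about 350 independent ones (2800/7.98), while the unclustered requirement is about 1,051.

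The 0.90 will be used when the trial is read. If the printed inputs were complete and right, a true 5-minute effect would more likely be missed than found at the planned size, and a null result read against 90% power would be taken as stronger evidence against the policy than it is.

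**Working it through.** **Inputs from the article:** power 0.90; effect 5 min; SD 25 min; ICC 0.2; CV 0.3 (read as the CV of preschool size); average size 35; 2800 children in 85 preschools, so 2800/85 = 32.9 per preschool; 1:1 allocation. **Assumed:** two-sided alpha 0.05 and no baseline adjustment.

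**1. Requirement for 90% power**
- Without clustering: N = 4 × (1.960 + 1.2816)² × 25² / 5² = 1,051 children.
- Design effect = 1 + ((1 + CV²) × m − 1) × ICC. With m = 35: 1 + (1.09 × 35 − 1) × 0.2 = 8.43.
- Need: 1,051 × 8.43 ≈ 8,860 children; 8,860 / 35 ≈ 253 preschools. The stated 2800 in 85 is not reproduced.

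**2. Power at the stated size**
- With m = 32.9: design effect = 1 + (1.09 × 32.94 − 1) × 0.2 = 7.98.
- SE = 25 × √(4 × 7.98 / 2800) = 2.67 min; 5 / 2.67 = 1.873.
- Power = Φ(1.873 − 1.960) = 46.5% (45.7% with a t reference on 83 df).
- Difference detectable at 90% power: 3.24 × 2.67 ≈ 8.7 min.

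**3. Limit with unlimited children per preschool**
- Between-preschool variance = 0.2 × 625 = 125. SE = √(4 × 125 / 85) = 2.43 min, and power is about 54%. This limit applies to the unadjusted comparison.

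**4. Other readings of the printed figures**

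| Reading | Power |
|---|---|
| One-sided 5% (or two-sided 10%) | 59% |
| CV ignored | 49.5% |
| m = 35, 2975 children (85 × 35) | 46.8% |
| Mixed-model weighting of unequal preschools | 49.1% |
| 85 preschools per arm, 2800 in total | 71% |
| 85 preschools and 2800 children per arm | 75% |

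The last two go against the Abstract, which gives 85 and 2800 as totals. None reaches 90%.

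**5. What would give 90% with 2800 in 85, changing one quantity at a time**
- ICC about 0.048.
- SD about 14.4.
- Baseline correlation r, if 25 is the SD of a level and the analysis adjusts for baseline: 25 × √(1 − r²) = 14.4, so r ≈ 0.82. By comparison, r = 0.5 gives 58% and r = 0.7 gives 75%.
- If 25 is already the SD of change, the printed figures offer no such gain. If it is the SD of a level and plain change scores are used, the SD of change is 25 × √(2(1 − r)), which equals 25 only at r = 0.5.

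**6. The sample that took part**
- The text with Fig. 1 reports 3775 children and 124 preschools at baseline (the 3775 is counted over the 127 that agreed). With 30% loss, about 2,640 children remain, or 21.3 per preschool.
- Design effect = 1 + (1.09 × 21.3 − 1) × 0.2 = 5.44; SE = 25 × √(4 × 5.44 / 2640) = 2.27 min. Power is about 60%, and the detectable difference at 90% is 3.24 × 2.27 ≈ 7.4 min.

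**The case against.** The strongest defence is an unreported gain from baseline measurement. The sizing "was projected with a change in MVPA as the main outcome variable", physical activity is measured at baseline and at 6 months, and the Statistical analysis section models pre-to-post change with mixed models. A condensed article could have dropped the correlation that was used.

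Nor is 0.82 as demanding as it looks. With ICC 0.2 and about 33 children per preschool, about 90% of the variance of a preschool mean lies between preschools (1.09 × 32.94 × 0.2 / 7.98 = 0.90), so the stability of preschool means over time dominates. For illustration, with assumed values of 0.85 at preschool level and 0.5 at child level, r = 0.90 × 0.85 + 0.10 × 0.5 ≈ 0.815 and power is about 90%.

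This stands as a possible explanation, but it does not make the section correct. No correlation is stated, the SD is not identified as that of a level, and the printed inputs are offered as the basis for the printed size.

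Two stronger conclusions are tempting. A reader might infer that 0.2 is a slip for 0.05, because ICC 0.05 with m = 35 and CV 0.3 gives a design effect of 2.86 and 3,002 children in 86 preschools. That is close but not exact: at the article's own 32.9 per preschool it gives about 2,885 in 88. Other single changes also give 90%. A reader might also infer that the trial has only 46% power. That holds only if the analysis takes nothing from baseline or 25 is already the SD of change, and the article settles neither.

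**Conclusion.** The section is wrong as written. Under an unadjusted comparison at two-sided 5%, the printed inputs give about 46% power against the stated 0.90, a shortfall of roughly threefold in children and preschools. No conventional alpha, sidedness or handling of cluster-size variation closes it. At least one printed input or the power is wrong, or an input that matters was left out; the article does not show which.

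The 46% and the 54% limit rest on three assumptions: two-sided 5%, no baseline adjustment (or 25 as the SD of change), and, for the 46% only, CV 0.3 as variation in preschool size. They describe what the printed figures imply and do not establish the power the trial will have.

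**What to change.** Check the calculation file, then correct the Sample size section and the Abstract's claim of adequate power in line with what it shows.

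- **(a) An ICC near 0.05 was used:** correct 0.2 and give the source of the value.
- **(b) A baseline correlation or a smaller SD was used:** state it, say whether 25 is the SD of a level or of change, and show that 0.90 follows.
- **(c) The printed inputs are complete and right:** replace 0.90 by about 46% for 85 preschools (about 60% for the 124 that took part, assuming 30% loss), and give the difference detectable at 90% power: about 8.7 min, or about 7.4 min with 124.

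In every case, state alpha and sidedness beside the corrected figure. Do not print 46% before (a) and (b) are ruled out, since that could replace one error with another.

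The cost is one rewritten paragraph and a matching change in the Abstract. Recruitment is complete and none is added. The downside is that the stated power may become less favourable.
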